If indicated by either surgeon or anaesthesiologist, all patients, irrespective of their group assignment, can receive boluses of open-label rocuronium 0.30 mg/kg. The reason for the on-demand bolus is registered. Surgical conditions will be scored immediately before and 5 min after a bolus when requested by the surgeon only, so as not to affect blinding of the surgeons. Indications for bolus infusion are high peak inflation pressure (>35 mm Hg), high abdominal (>15 mm Hg) and thorax (>8 mm Hg) insufflation pressure, and movement, breathing, or straining of the patient. Intra-abdominal pressure will be registered every 30 min from the abdominal CO_2_ insufflation device.

For neuromuscular function monitoring, the TOF-watch SX acceleromyograph (MSD BV, Haarlem, The Netherlands) will be used. During the procedure, a TOF count (situated at the flexor hallucis brevis of the leg) will be done every 30 min at the same time as the evaluation of the surgical conditions and directly before and 5 min after an on-demand bolus [10]. Both the anaesthesiologist and the surgeon will be blinded for the results of this measurement.

When the operation is finished, a TOF count and ratio are done at the ulnar nerve (not blinded). Depth of NMB will be scored as follows: (1) very deep NMB (post-tetanic count, no twitches, (2) deep NMB (post-tetanic count, one or two twitches), (3) moderate NMB (TOF, one or two twitches), and (4) shallow or no NMB (TOF four twitches, ratio of more than 0 %). In patients with a very deep or deep NMB, a TOF is repeated 30 min after infusion of sugammadex to check for recurarization. Based on the TOF count at the end of operation, sugammadex is given at a dose of 16 mg/kg in very deep block, 4 mg/kg in deep NMB, 2 mg/kg in moderate NMB, and 2 mg/kg in shallow NMB. If recurarization is found, an additional dose of sugammadex is given on the basis of the TOF count found at that time. In case of a clinical reason to continue mechanical ventilation after surgery, administration of sugammadex is postponed until one post-tetanic twitch is found. The sugammadex dose needed in case of a very deep block (16 mg/kg) was added to the protocol after 10 patients.

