#### Secondary parameters

Rating of SRS during thoracic phase of the operation, number of on-demand boluses infused, and indication of on-demand bolus administration.Rating of anaesthesia conditions, including peak and mean respiratory pressures and incidence peak insufflation pressure of more than 35 mm Hg; depth of NBM at the end of surgery, intraoperative cardiac and respiratory incidents; and time until spontaneous breathing and time until extubation after interruption of sedation.Costs: amount of rocuronium used (milligrams), dose of sugammadex needed (milligrams) to reach a TOF of more than 90 %, time to reversal, number of patients (percentage) with recurarization measured 30 min after reversal and consequently the need for additional sugammadex, and duration of surgery and operating room occupancy (expressed in hours and personnel cost per hour) and ICU stay.Perioperative surgical complications.The ability of surgeons and anaesthesiologists to estimate post-operatively to which group the patient was randomly assigned (at the end of each of the two phases).

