### Statistical analysis

The data analysis will be based on an intention-to-treat approach. Baseline continuous variables will be summarized by using mean with SD or median with interquartile range as appropriate. Categorical variables will be summarized by using percentage and number of patients. The SRS will be measured repeatedly. These repeated measurements will be summarized to a mean for every patient. These values will follow a normal distribution and therefore be tested by using a Student’s *t* test. A two-sided *P* value of less than 0.05 will be considered statistically significant. The difference in SRS between the two groups will further be examined by using a general linear model. Covariates will be analyzed univariately. Covariates will be included in a multivariable analysis if the univariate *P* value is less than 0.20. A backward selection process will be used to achieve the most optimal model.

Covariates to be considered are anaesthesia- or surgery-related (for example, timing of abdominal and thoracic phase, drug dosages, use of epidural anaesthesia, and duration of surgery) and patient-related (for example, surgical history, age, weight, and body mass index). Patients with less than three surgical rating scores because of early termination of the surgical procedure will be excluded in a secondary analysis. Additional analyses will be performed on the secondary outcome parameters. No interim analysis will be done; the study will be terminated after enclosure of the last patient. Because of the amendment in sugammadex dose, the first 10 patients will be excluded for the cost analysis only. A sensitivity analysis, including the first 10 patients, will be performed.

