### Limitations

This study has some unavoidable limitations instigated by the included surgical population and chosen design. During these procedures, TOF count is not reliable in prone positioning and supine positioning, because of the movement confinement of the body. Although this is part of the normal situation anaesthesiologists face during these procedures, we cannot be absolutely sure whether the patients randomly assigned to receive deep neuromuscular relaxation are insufficiently relaxed or too deeply relaxed. Indeed, for adequate neuromuscular relaxation of the diaphragm, a post-tetanic count of between 0 and 1 is probably necessary and this is very hard to accomplish in normal practice. We will use the standard dosing for continuous use that is advised in the product specifics (Summary of Product Characteristics text) of rocuronium and sugammadex. However, because of the lack of data on continuous administration for more than 5 h, there may be variability in NMB seen, and some patients may have a very deep block at the end of the procedure. We therefore amended the protocol after 10 patients, more clearly describing the management of patients with a very deep block at the end of the operation. In addition, we use the peroneal nerve to measure TOF because we expect less movement inhibition. However, it is possible that, owing to positional problems, we cannot get a reliable TOF for every patient. Consequently, we do not adjust the infused rocuronium dose on the basis of these measurements.

Another limitation is that the surgeons might guess in which group the patient is randomly assigned because of high abdominal pressures, respiratory events, or diaphragm movements. This might influence scoring of SRS. A recent study, however, showed that surgeons were not able to estimate the group assignment to deep versus moderate neuromuscular relaxation. They estimated correctly in a little more than 50 % and this can also be explained by chance. We also let the surgeons estimate group assignment to be able to estimate bias in SRS. In addition, we chose for a neuromuscular regime that is common practice (on demand) and compared that with a regime that is not (deep neuromuscular relaxation). Based on the results of the present study we will weigh benefits against costs.

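### Leaving out the first 10 patients follows the cost label, not the outcomes that the sugammadex amendment can affect

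*Protocol article*

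**What the plan says.** All references are to the protocol article.

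- **Statistical analysis.** The section opens with the general principle: "The data analysis will be based on an intention-to-treat approach". It ends with an exception made because of the sugammadex amendment, under which the 10 earliest "patients will be excluded for the cost analysis only". The next sentence adds: "A sensitivity analysis, including the first 10 patients, will be performed".
- **Study procedures and measurements.** On what changed: "The sugammadex dose needed in case of a very deep block (16 mg/kg) was added to the protocol after 10 patients". The same section has the sugammadex dose chosen from a train-of-four (TOF) measurement taken once the operation is over.
- **Limitations.** The amendment, which concerns the close of the operation, is described again: "We therefore amended the protocol after 10 patients, more clearly describing the management of patients with a very deep block at the end of the" […]. This section also says that the rocuronium infusion is not adjusted to the intraoperative TOF readings.
- **Secondary parameters, cost item.** It lists milligrams of rocuronium, sugammadex dose, time to reversal, recurarization, "and duration of surgery and operating room occupancy", and ICU stay.
- **Secondary parameters, anaesthesia-conditions item.** It lists "time until spontaneous breathing and time until extubation after interruption of sedation".
- **Abstract.** Costs are described in euros and tied to rocuronium, sugammadex and surgery duration.
- **Discussion.** Time to extubation is part of the question that the cost analysis is meant to answer.

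**The concern.** The stated reason for leaving out 10 randomised patients is a change in reversal. Such a reason supports excluding them from outcomes that come after reversal and can be altered by it, and from no others. The rule is instead attached to a heading that mixes both kinds of outcome, and the word *only* closes it to outcomes under other headings.

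Two things are at stake, both among secondary outcomes. First, rocuronium use and surgery duration may be compared in fewer patients than were randomised, for a reason that does not apply to them. Surgery duration is a possible benefit that the article intends to weigh against drug costs. Second, the times to spontaneous breathing and extubation may combine patients managed before and after the amendment, with no planned look at whether that matters.

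**Working it through.** **1. The plan's own numbers.** Inputs from Sample size calculation: difference 0.6, SD 0.7, two-sided alpha 0.05, power 90%. The normal approximation is n = 2 × (1.960 + 1.282)² × (0.7/0.6)² ≈ 28.6, so 29 per group. The exact t-test calculation gives 29.6, so 30 per group and 60 in total, with power 0.904. Adding 10% gives 60 × 1.10 = 66. The stated 60 and 66 are reproduced. They serve here only as denominators.

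**2. Which outcomes the amendment can reach.**

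| Outcome | Listed under | Can it depend on reversal? | First 10, read literally |
|---|---|---|---|
| Rocuronium used | Costs | No | Out |
| Surgery duration | Costs | No | Out |
| Sugammadex dose, time to reversal, recurarization | Costs | Yes | Out |
| Operating-room occupancy, ICU stay | Costs | Possibly | Out |
| Time to spontaneous breathing, time to extubation | Anaesthesia conditions | Possibly | In |

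The two *No* entries follow from the timing: sugammadex is dosed after the operation has finished, and neither description of the amendment mentions the rocuronium infusion. The last row rests on the Background, which links a deep block at the end of surgery to slower emergence and links reversal to faster extubation.

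**3. Precision lost for rocuronium use and surgery duration.** With unchanged variance and a balanced loss, the standard error scales with 1/√N.

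- 66 analysed: 10/66 = 15.2% lost, 56 left, √(66/56) = 1.086, so 8.6% wider.
- 60 evaluable, with all of the first 10 among them: 10/60 = 16.7% lost, 50 left, √(60/50) = 1.095, so 9.5% wider.

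**4. Extent of mixing in the extubation times.** At most 10 of 66 patients (15.2%) predate the amendment. The change concerns very deep block only, so the affected patients are those of the 10 who had one. The article gives neither their number nor how they were managed. The affected share therefore lies between 0 and 15.2%, and no direction or size of bias can be derived.

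**5. The boundary of the cost analysis.** Time to extubation is an anaesthesia condition under Secondary parameters but belongs to the cost question in the Discussion. It could thus be analysed with the first 10 in one place and without them in the other.

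**The case against.** Several objections carry weight.

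- **The sensitivity analysis already restores the 10.** For the cost items it does, and this stands. But the restored result is secondary and the reduced set remains the main one. For the extubation times the useful check is the opposite, an analysis without the 10, and none is stated.
- **The cost analysis may mean only the euro total.** This is possible. A total cost per patient needs one patient set across its components, and leaving the 10 out of it is coherent. On that reading rocuronium use and surgery duration lose nobody as separate outcomes. The loss above is therefore an upper figure under a literal reading of the Abstract and Secondary parameters. The article does not settle which reading applies.
- **Keeping all patients in the extubation outcomes is intention to treat.** This stands, and the first 10 should not leave the main analysis of those outcomes.
- **An article leaves detail to the full protocol or analysis plan.** True of omissions. Here the article states a rule and limits it with the word *only*.

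A reader might infer that about 15% of extubation times in the continuous-infusion group come from a superseded reversal rule and that the comparison is biased. The documents do not support this. They say that a dose for very deep block was added and its management described more clearly, show no change for the other depths of block, and do not report how many early patients had a very deep block. Sugammadex is also postponed when ventilation continues for clinical reasons, which may dilute any effect. Nor is the exclusion as a whole without reason: it fits the sugammadex outcomes and may partly fit operating-room occupancy and ICU stay.

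**Conclusion.** The point holds as a minor one, confined to secondary outcomes. The exclusion is tied to a label and not to what the amendment can change. Read with the Abstract and Secondary parameters, it costs the main comparison of rocuronium use and surgery duration up to 10 of 66 patients and an 8.6% wider standard error (9.5% with 60 evaluable), assuming equal variance and a balanced loss. For time to spontaneous breathing and time to extubation, what is missing is a check, and the documents show no error of known size. That an effect on these times is possible is an inference from the Background; the article does not state it. The primary endpoint, surgical rating in the abdominal phase, is recorded before reversal and is not touched. No view is taken on the sugammadex doses.

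**What to change.** Replace the single exclusion sentence with a short list by outcome:

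1. **All randomised patients:** rocuronium used and surgery duration, each analysed as an outcome in its own right.
2. **Without the first 10, with the planned all-patient sensitivity analysis:** sugammadex dose, time to reversal, recurarization and total cost.
3. **Intention to treat as the main analysis, plus a sensitivity analysis without the first 10:** time to spontaneous breathing, time to extubation, operating-room occupancy and ICU stay.

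The cost is a few sentences and a few extra sensitivity analyses. It needs no new data, no additional patients and no change to treatment.

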## Discussion

This study is the first to evaluate the benefits of deep neuromuscular relaxation during thoracolapascopic esophageal surgery. In addition, this type of surgery is unique in that it consists of both an abdominal and a thoracic phase and because of its long duration, enabling acquisition of an adequate number of SRS scores. Considering the results of earlier studies, we can expect a benefit in operating conditions of deep neuromuscular relaxation during the abdominal phase. However, whether the operation is started with the abdominal or thoracic phase may influence SRS scores because of cumulative doses of anaesthetics in a later phase. Therefore, the benefit may be smaller when the abdominal phase comes last. To better determine this influence, patients are randomly assigned in blocks. Whether a benefit can be found during the thoracoscopic phase has yet to be determined. The ribcage will keep the surgical field open, and the diaphragm may be the only influence on surgical conditions. In addition, as this operation normally takes 8 h, deep neuromuscular relaxation may shorten duration of operation. However, this benefit may be counteracted by the costs of rocuronium and sugammadex and time until extubation. A cost analysis will be done to answer this question.

We will use the same scoring system as was developed by Martini et al. [2]. It showed adequate reliability in discrimination between surgical conditions and a low variability between surgeons. The scoring will be performed by two surgeons with ample experience with the procedure, and both are trained in SRS scoring before the start of the study. In contrast to Martini et al., we chose not to include the anaesthesiologist in the SRS scoring, because of lack of expertise in assessing the quality of the (laparoscopic/thoracoscopic) surgical field. Anaesthesiologists will assess the anaesthesia conditions (peak and mean respiratory pressures, incidence peak insufflation pressure of more than 35 mm Hg, depth of NBM at the end of surgery, intraoperative cardiac and respiratory incidents, and the indication for on-demand neuromuscular blocking agent).

The reasons for anaesthesiologists not to standardize a deep NMB regime may be the expected need for reversal at the end of the procedure. When employing deep NMB, one has the option to use sugammadex, which is costly, or have the patient on mechanical ventilation post-operatively, which may increase the incidence of pneumonia following surgery [1]. Reversal with (high-dose) neostigmine is usually not favored following these procedures in fear of the cholinergic effects on the newly formed anastomosis, although recent evidence for the adverse effects on anastomotic patency is scarce and the existing data are conflicting [6–8].

Sugammadex has been shown to be a safe and fast alternative to reverse the neuromuscular blocking induced by rocuronium, even when it was administered continuously for up to 5 h [11]. However, as yet, no data on the use of sugammadex after 8–9 h of deep (continuous) neuromuscular relaxation and the incidence of recurarization exist. Therefore, we will register time until TOF of more than 90 % and the incidence of recurarization.

Furthermore, lack of adequate neuromuscular monitoring (e.g., TOF)—in the prone position but especially in the supine position, where both hands are tucked in alongside the body—is challenging to the anaesthesiologist. Hand movements are often inhibited, and TOF counts are unreliable. In view of that, anaesthesiologists and surgeons often disagree about the operating conditions and the ability of the surgeons to judge whether the patient is adequately relaxed or not. We therefore let the surgeons (and anaesthesiologist) “estimate” at the end of the operation to which group the patient was randomly assigned.

### Limitations

This study has some unavoidable limitations instigated by the included surgical population and chosen design. During these procedures, TOF count is not reliable in prone positioning and supine positioning, because of the movement confinement of the body. Although this is part of the normal situation anaesthesiologists face during these procedures, we cannot be absolutely sure whether the patients randomly assigned to receive deep neuromuscular relaxation are insufficiently relaxed or too deeply relaxed. Indeed, for adequate neuromuscular relaxation of the diaphragm, a post-tetanic count of between 0 and 1 is probably necessary and this is very hard to accomplish in normal practice. We will use the standard dosing for continuous use that is advised in the product specifics (Summary of Product Characteristics text) of rocuronium and sugammadex. However, because of the lack of data on continuous administration for more than 5 h, there may be variability in NMB seen, and some patients may have a very deep block at the end of the procedure. We therefore amended the protocol after 10 patients, more clearly describing the management of patients with a very deep block at the end of the operation. In addition, we use the peroneal nerve to measure TOF because we expect less movement inhibition. However, it is possible that, owing to positional problems, we cannot get a reliable TOF for every patient. Consequently, we do not adjust the infused rocuronium dose on the basis of these measurements.

Another limitation is that the surgeons might guess in which group the patient is randomly assigned because of high abdominal pressures, respiratory events, or diaphragm movements. This might influence scoring of SRS. A recent study, however, showed that surgeons were not able to estimate the group assignment to deep versus moderate neuromuscular relaxation. They estimated correctly in a little more than 50 % and this can also be explained by chance. We also let the surgeons estimate group assignment to be able to estimate bias in SRS. In addition, we chose for a neuromuscular regime that is common practice (on demand) and compared that with a regime that is not (deep neuromuscular relaxation). Based on the results of the present study we will weigh benefits against costs.

## Trial status

Approval of the protocol has been obtained, and recruitment of the patients has started. The study end is planned in June 2016.

## Abbreviations

ASA: American Society of Anesthesiologists
ICU: Intensive care unit
i.v.: Intravenous
NMB: Neuromuscular block
PACU: Post-anaesthesia care unit
SD: Standard deviation
SRS: Surgical rating scale
TOF: Train-of-four
